# Live and Recorded Music Interventions to Reduce Postoperative Pain: Protocol for a Nonrandomized Controlled Trial

**DOI:** 10.2196/40034

**Published:** 2023-03-10

**Keywords:** live music intervention, recorded music intervention, pain VAS, postsurgical pain, neuroinflammation, pain management, intervention, music, postoperative, pain, perception, pain relief, live music, recorded music, music intervention, music, pain perception

## Abstract

**Background:**

Postoperative patients who were previously engaged in the live musical intervention Meaningful Music in Healthcare reported significantly reduced perception of pain than patients without the intervention. This encouraging finding indicates a potential for postsurgical musical interventions to have a place in standard care as therapeutic pain relief. However, live music is logistically complex in hospital settings, and previous studies have reported the more cost-effective recorded music to serve as a similar pain-reducing function in postsurgical patients. Moreover, little is known about the potential underlying physiological mechanisms that may be responsible for the reduced pain perceived by patients after the live music intervention.

**Objective:**

The primary objective is to see whether a live music intervention can significantly lower perceived postoperative pain compared to a recorded music intervention and do-nothing control. The secondary objective is to explore the neuroinflammatory underpinnings of postoperative pain and the potential role of a music intervention in mitigating neuroinflammation.

**Methods:**

This intervention study will compare subjective postsurgical pain ratings among 3 groups: live music intervention, recorded music intervention, and standard care control. The design will take the form of an on-off nonrandomized controlled trial. Adult patients undergoing elective surgery will be invited to participate. The intervention is a daily music session of up to 30 minutes for a maximum of 5 days. The live music intervention group is visited by professional musicians once a day for 15 minutes and will be asked to interact. The recorded music active control intervention group receives 15 minutes of preselected music over headphones. The do-nothing group receives typical postsurgical care that does not include music.

**Results:**

At study completion, we will have an empirical indication of whether live music or recorded music has a significant impact on postoperative perceived pain. We hypothesize that the live music intervention will have more impact than recorded music but that both will reduce the perceived pain more than care-as-usual. We will moreover have the preliminary evidence of the physiological underpinnings responsible for reducing the perceived pain during a music intervention, from which hypotheses for future research may be derived.

**Conclusions:**

Live music can provide relief from pain experienced by patients recovering from surgery; however, it is not known to what degree live music improves the patients’ pain experience than the logistically simpler alternative of recorded music. Upon completion, this study will be able to statistically compare live versus recorded music. This study will moreover be able to provide insight into the neurophysiological mechanisms involved in reduced pain perception as a result of postoperative music listening.

**Trial Registration:**

The Netherlands Central Commission on Human Research NL76900.042.21; https://www.toetsingonline.nl/to/ccmo_search.nsf/fABRpop?readform&unids=F2CA4A88E6040A45C1258791001AEA44

**International Registered Report Identifier (IRRID):**

PRR1-10.2196/40034

## Introduction

In recent research, postoperative patients exposed to a live musical intervention reported significantly reduced perception of pain than patients without the intervention [1]. This encouraging finding indicates a potential for postsurgical musical interventions to have a place in standard care as therapeutic pain relief. However, live music is logistically complex in hospital settings, and previous studies have reported the more cost-effective *recorded* music to serve as a similar pain-reducing function in postsurgical patients [2,3]. Therefore, this study primarily aims to compare the effectiveness of postoperative live versus recorded music interventions in reducing patients’ perception of postsurgical pain. In order to potentially expand this finding from subjective to objective metrics, secondary outcomes will explore whether subjective pain perception is statistically related to more objective metrics such as pain medication dosage or respiration rate [4].

Although previous findings showed a convincing influence of music intervention on postsurgical pain perception [1-3,5-7], the physiological mechanisms that could make this possible are not yet understood [8]. It has been reported that music modulates psychoneuroimmunology [9,10] such as lowering stress-induced cortisol [11] and enhancing neurogenesis [12]. While chronic or long-term postsurgical pain has established links to neuroinflammation [13,14], the possibility exists that immediate postsurgical pain—before it reaches a chronic state—may have links to neuroinflammation as well [15]. Thus, one possibility is that music is mitigating postsurgical neuroinflammation, which could in turn be affecting the immediate postsurgical pain.

Therefore, further secondary outcomes will explore behavioral indicators (postoperative cognitive decline or POCD and delirium) and biological markers (interleukin-6 [IL6], C-reactive protein [CRP], neutrophil gelatinase–associated lipocalin [NGAL], and translocator protein [TPSO]) with established neuroinflammatory underpinnings [16-20] to see whether the primary pain outcome has a statistical relationship to these neuroinflammatory-related metrics. The exploratory electroencephalogram (EEG) analyses will also be conducted to see whether either entropy [21], alpha power [22], or delta/alpha power ratio [23,24] can provide neuroinflammatory markers, which could correlate with postoperative pain outcomes. Finally, we will explore whether these neuroinflammatory markers seem to be mitigated by either the live music or active control intervention to explain the reduced pain reported by postsurgical patients in music intervention studies [2,20].

The primary objective is to see whether a live music intervention reduces pain perception compared to both recorded music active control and standard care control groups. The secondary objective is to explore the role of music in mitigating the neuroinflammatory response to surgery, for future hypothesis-directed research.

## Methods

### Study Design

The study will take place at the University Medical Center Groningen (UMCG), which has already hosted the Meaningful Music in Healthcare (MiMiC) live intervention [25]. The intervention study follows an on-off nonrandomized controlled trial (NCT) design [26]. The NCT is necessary for this particular intervention in practice because the live music intervention cannot easily be randomized to skip patients in the same ward without them hearing the music or seeing the musicians as they play for other patients and nurses.

In this NCT design, treatments and data collection will be conducted in 15 blocks over the course of 4 years. According to the 29-day treatment block, the three 5-day treatments (live music intervention, recorded music active control intervention, and standard care control) will be offered with a 7-day washout between treatments. The washout will minimize the number of participants whose hospital stay overlaps with another treatment. Based on the previous research (UMCG research register 201600541), we expect approximately 8 full data sets per 5-day treatment block.

Note that while the intended outcome of the music intervention is therapeutic (eg, experiencing reduced pain), the music intervention is conducted by conservatory-trained music practitioners but not by music therapists. Music therapists are licensed therapists who have a degree in music therapy including clinical training. The music practitioners in this study are primarily professional musicians who have taken 1 music-conservatory course and several internships to train them for clinical settings but they are not therapists.

Design procedures are chronologically displayed in Figure 1. Preoperative questionnaires will be collected to assess cognitive function (6-item cognitive assessment [6CIT]) [27,28] and musical background (excerpt from the Dutch Musical Background Questionnaire [DMBQ]) [29,30]. Postoperative data collection procedures per day of treatment include pain visual analog scale (VAS) ratings, heart rate (HR), and blood pressure measuring 4 times a day (before, directly after, 3-hour, and 6-hour postintervention). EEG electrodes will be applied once in the morning and 4 EEG recordings will be collected with VAS ratings, HR, and blood pressure (before, during, 3-hour, and 6-hour postintervention). A blood sample will be collected once daily and integrated with standard care as far as possible (eg, if blood is drawn as part of standard care, the sample will be collected from the same needle). A schedule of assessments may be found in Table 1. Daily dosage of pain medication as well as any incidence of delirium (delirium observation screening scale [DOSS]) [31] or POCD will be collected.

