### Treatment Allocation

This study will take the form of an on-off NCT [26]. An on-off NCT takes into account real-world setting limitations of certain intervention types and allocates participant inclusion by alternation. The main reason for this is that MiMiC is a well-researched intervention, whose practical implementation is not suited for randomly selected participants to not participate. On the one hand, musicians will visit the nurses’ station and play music in various rooms around the ward; thus, it is not possible to prevent participants who may be allocated non-MiMiC treatment from hearing the live music. On the other hand, a central tenet of the MiMiC intervention is inclusion and participation, thus “rejecting” patients who would want to participate in music they hear on the ward, on the basis of trial group allocation, goes against the spirit of the intervention.

In contrast, the NCT relies on the randomness of who is scheduled for surgery during a given intervention week but does not exclude any patient from the activity being conducted (listening to live or recorded music). Therefore, the treatment schedule (live music intervention, recorded music active control, and standard care control) will be predetermined months in advance, and the patients included will be offered whichever treatment is occurring during their hospital stay. The patients will, however, be asked for their consent before they are informed which treatment will be offered during their surgery recovery. This will attempt to prevent patients who are initially biased for inclusion based on their affinity to music or not.

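### The stated 29-day block starts the three treatments on three different weekdays, which does not fit the argument that patients in different intervention weeks are comparable

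*Protocol article*

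**What the plan says.** The Study Design section fixes the calendar. It opens the description with "According to the 29-day treatment block" and states that "the three 5-day treatments" "will be offered with a 7-day washout between treatments". Treatment and data collection are "conducted in 15 blocks over the course of 4 years", and for each treatment period "we expect approximately 8 full data sets per 5-day treatment block".

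The Treatment Allocation section makes that calendar the allocation mechanism: "the patients included will be offered whichever treatment is occurring during their hospital stay". It justifies comparability by saying that "the NCT relies on the randomness of who is scheduled for surgery during a given intervention week". The schedule is set months ahead.

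The Abstract describes the intervention as "a daily music session of up to 30 minutes for a maximum of 5 days", so the number of sessions depends on how a patient's stay overlaps the treatment window.

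Postoperative day is listed under Other Study Parameters. The primary model contains group and time point only; baseline parameters enter in post hoc analyses. The article does not give the opening weekday of a block, the order of treatments over blocks, the operating weekdays or the distribution of length of stay.

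**The concern.** In a nonrandomised alternating design, the case for comparable arms is that the treatment windows are alike except for the treatment. If the windows cover different parts of the week, they can differ in ward staffing and activity. Where elective surgery follows the working week, they can also catch patients at different stages of recovery and for different numbers of sessions.

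Recovery stage bears on pain, medication use and the inflammatory markers; the Limitations section itself notes that marker readings depend on the time since the medical event. If the same treatment always fell in the same kind of window, recruiting more patients would not remove the difference.

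**Working it through.** **Inputs from the Study Design section.** Three 5-day treatments, two 7-day washouts, a 29-day block, 15 blocks, 4 years.

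**1. Reproduce the block length.** 5 + 7 + 5 + 7 + 5 = 29, as stated. The 5 and 7 days therefore run consecutively and in the same unit.

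**2. Start days.** Each treatment starts 5 + 7 = 12 days after the one before, so the offsets are 0, 12 and 24. Modulo 7 these are 0, 5 and 3: three different weekdays whatever the opening day.

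**3. Weekend days in the three windows, in calendar days.**

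| Block opens | First | Second | Third | Weekend days |
|---|---|---|---|---|
| Mon | Mon-Fri | Sat-Wed | Thu-Mon | 0/2/2 |
| Tue | Tue-Sat | Sun-Thu | Fri-Tue | 1/1/2 |
| Wed | Wed-Sun | Mon-Fri | Sat-Wed | 2/0/2 |
| Thu | Thu-Mon | Tue-Sat | Sun-Thu | 2/1/1 |
| Fri | Fri-Tue | Wed-Sun | Mon-Fri | 2/2/0 |
| Sat | Sat-Wed | Thu-Mon | Tue-Sat | 2/2/1 |
| Sun | Sun-Thu | Fri-Tue | Wed-Sun | 1/2/2 |

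The three counts are never all equal.

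**4. Working-day reading.** If the 5, 7 and 29 are working days, the offsets modulo 5 are 0, 2 and 4. A Monday opening then gives starts on Monday, Wednesday and Friday. Each treatment covers every working day once, but the second and third are interrupted by a weekend.

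**5. Sessions and postoperative day (illustration).** Assumptions, none given in the article: operations equally likely Monday to Friday, a block opening on Monday, calendar days, and a session on every treatment day on which the patient is in hospital from postoperative day 1 to the end of the stay. Results are for the windows Mon-Fri / Sat-Wed / Thu-Mon.

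If patients already in hospital when the window opens are included:
- 1-day stay: 1.0/1.0/1.0 sessions.
- 3-day stay: total sessions over the five contributing operating days are 10, 9 and 12, so the means are 10/5 = 2.0, 9/5 = 1.8 and 12/5 = 2.4. The first session falls on postoperative day 1 for 80%/60%/60%.
- 5-day stay: 16/7 = 2.3, 18/7 = 2.6 and 19/5 = 3.8 sessions. Mean postoperative day at first session is 2.29/2.43/1.6.

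If only patients operated on within the window are included, the first session is on postoperative day 1 in every window. Sessions for a 5-day stay are then 10/4 = 2.5, 3/2 = 1.5 and 7/2 = 3.5.

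**6. Over the trial.** There are 15 × 5 = 75 treatment days per arm. With every block opening on Monday in a fixed order, weekend days per arm are 0/30/30. With cyclic rotation each arm takes each position 5 times: 5 × (0 + 2 + 2) = 20 per arm.

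**7. Alignment.** Weekdays match only if 5 + gap is a multiple of 7. A 9-day gap gives 14, and a block of 5 + 9 + 5 + 9 + 5 = 33 days. Total block time goes from 15 × 29 = 435 to 15 × 33 = 495 days, against about 1,461 days in 4 years.

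**The case against.** The other side has five arguments.

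- *The unit is not stated.* Working days also sum to 29, and then no treatment day falls on a weekend. This stands against the weekend counts, but the starts still fall on three different weekdays.
- *The article may be loosely worded.* Alternate Monday-to-Friday weeks would fit the term intervention week. They imply a 9-day gap and a 33-day block, however, so the stated 7 and 29 would then need correcting.
- *Confounding by arm is not shown.* A reader might infer that the imbalance lines up with arm in all 15 blocks. The documents do not support that. It needs a fixed order and a pattern of opening weekdays that does not average out; neither is stated, and a full calendar may settle both. Rotation gives 20/20/20. Even with a fixed order, blocks run back to back would move the opening weekday by one each time (29 is 1 modulo 7), and after 14 blocks each arm would have 20 weekend days.
- *Differences in recovery stage and sessions are assumed.* A reader might also infer that postoperative day and session counts do differ between arms. That rests on an operating schedule and lengths of stay that the article does not give. Sessions do not differ for 1-day stays, and the first-session day does not differ if only patients operated on within the window enter.
- *The primary test gives some protection.* It concerns the course over four ratings within a day, the first taken before the intervention, so a constant difference in pain level cancels. Only a different within-day course would bias it, and no size can be given. Level comparisons, such as medication dose and delirium incidence, lack that protection. Postoperative day is at least recorded and can be examined post hoc.

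These arguments limit the consequences. They do not remove the weekday shift within each block.

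**Conclusion.** The point holds as a should-fix matter. It is certain from the stated figures that the three treatments in every block start on three different weekdays. In calendar days the weekend mix is also unequal in every block. This conflicts with the like-for-like intervention week on which the article relies.

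The rest is conditional. Under the assumptions shown, mean sessions range from no difference for 1-day stays to 2.3/2.6/3.8 for 5-day stays with patients already in hospital included, or 2.5/1.5/3.5 with only patients operated on in the window. Trial-wide confounding is possible but not established. Any bias in the primary group-by-time test is unquantified and may be small.

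**What to change.** - Replace the 7-day gap with a 9-day gap, so that each treatment covers the same five weekdays (for example Monday to Friday in weeks 1, 3 and 5) in a 33-day block. If alternate Monday-to-Friday weeks are already what is meant, correct the 7-day and 29-day figures instead.
- Rotate treatment order with a 3×3 Latin square, using each of its three orders in 5 of the 15 blocks, and state the order and opening weekday.
- For blocks already run, add a sensitivity analysis adjusting for start weekday and the postoperative day already being recorded.

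The cost is 4 days per block, or 15 × 4 = 60 calendar days over the trial, within the planned 4 years and with no extra patients or staff. The longer gap also serves the stated aim of limiting overlapping stays. Only 5 participants had been recruited at submission, so nearly all of the data were then still to be collected.

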**Figure 1 figure1:**
[figure not shown]
Chronological walk-through of the design procedures. After entering the ward, subsequent steps repeat per each day of treatment. Blood sample, blood pressure, and heart rate are part of standard care measurements and will be incorporated with standard care whenever possible. 6CIT: 6-item cognitive assessment; DMBQ: Dutch Musical Background Questionnaire; fEEGrid: face electrode grid for electroencephalogram recordings; MiMiC: Meaningful Music in Healthcare; VAS: visual analog scale.

**Table 1 table1:** Schedule of procedures.

Time		Procedures	Duration (minutes)
Preoperative		Six-item cognitive assessment Dutch Musical Background Questionnaire excerpt	7.5 and 4.5 (total 12)
**Postoperative**			
	9 AM	fEEGrid^a^ preparation and placement Respiration biosensor placement Blood vial^b^	10
	10:30 AM	VAS^c^ rating, HR^d^, respiration rate, blood pressure, and start EEG^e^ recording	5
	10:40-11 AM	MiMiC^f^ or recorded music or no intervention VAS rating, HR, respiration rate, blood pressure, and stop EEG recording	20
	2 PM	VAS rating, HR, respiration rate, blood pressure, and EEG recording	15
	5 PM	VAS rating, HR, respiration rate, blood pressure, and EEG recording	15
	5:15 PM	Remove fEEGrid and respiration biosensor	5
	Total	N/A^g^	70

^a^fEEGrid: face electrode grid for EEG recordings.

^b^The blood vial collection will be integrated into standard care as much as possible, thus, the time may not be 9 AM if other blood collection is at a different time.

^c^VAS: visual analog scale.

^d^HR: heart rate.

^e^EEG: electroencephalogram.

^f^MiMiC: Meaningful Music in Healthcare.

^g^N/A: not applicable.

### Population (Base)

The study will include patients who have undergone elective surgery in the UMCG and are hospitalized for at least 1 day following surgery. All patients must be 18 years or older and able to make their own decisions. Patients must further be able to hear music with normal or corrected normal hearing (ie, a hearing aid).

### Inclusion Criteria

In order to be eligible to participate in this study, a subject must meet all of the following criteria: (1) 18 years or older, (2) postsurgery hospitalization (all surgery types), (3) elective surgery, (4) able to hear music, (5) able to give informed consent, and (6) able to communicate.

### Recruitment

Patients will be informed as soon as the date of hospital admission is set in the weeks that the study is planned. The patient will receive an information letter and informed consent from the provider or it will be sent to them by email. A member of the research team will contact the patients after a minimum of 24 hours for participation and answer possible questions. Patients will have up to the time of their surgery to decide, allowing for time to fill out the preoperative questionnaires. Consent can be withdrawn at any time at which point all data collection and treatment will stop.

### Ethics Approval

This protocol has been approved by the Central Medical Ethics Committee of the UMCG (METc2021.359) and is registered with the Netherlands central commission of human research (CCMO-register number NL76900.042.21). The informed consent letter is written in plain, nonacademic Dutch with no medical jargon. Only pseudoanonymized (deidentified) data will be published. Patients participating in the study will receive a small token gift (such as a hand lotion or lip balm).

### Study Parameters and End Points

#### Main Study Parameter and End Point

Subjective pain ratings are determined with a VAS rating (0-10) [1].

#### Secondary Study Parameters and End Points

The secondary study parameters (Table 2) and end points are as follows: (1) objective pain metric (volume of administered pain medication); (2) respiratory rate and tidal volume; (3) HR; (4) blood pressure; (5) neuroinflammation blood markers (IL6, NGAL, CRP, and serum TPSO); (6) behavioral indicators of neuroinflammation (delirium [31] and POCD incidence); and (7) EEG markers of neuroinflammation (alpha power, delta/alpha power ratio, and entropy).

**Table 2 table2:** Secondary study parameters.

Outcome	Metric	Statistics
Objective pain measure	Pain medication dosage (ccs)	Chi-square test
Neuroinflammation, blood markers	IL6^a^, NGAL^b^, CRP^c^, and serum TPSO^d^	*F* test (RM^e^ ANOVA, pre-post)
Neuroinflammation, behavioral indication	Incidence delirium and incidence POCD^f^	*F* test (one-way ANOVA)
Neuroinflammation, EEG^g^ indication	Alpha power, alpha/delta power, and entropy	*F* test (RM ANOVA same as primary)
Neuroinflammation, physiological	HR^h^, respiration rate, and blood pressure	*F* test (RM ANOVA same as primary)

^a^IL6: interleukin-6.

^b^NGAL: neutrophil gelatinase–associated lipocalin.

^c^CRP: C-reactive protein.

^d^TPSO: translocator protein.

^e^RM: repeated measures.

^f^POCD: postoperative cognitive decline.

^g^EEG: electroencephalogram.

^h^HR: heart rate.

